Treatment with syndrome differentiation is one of the characteristics of the traditional Chinese medicine (TCM) theoretical system, and it is advantageous in the treatment of COPD and has achieved significant effects. “Phlegm-heat congested lung” is one of the major features of COPD.^[10]^ The TCM for clearing heat and resolving phlegm often achieves good effects in the treatment of AECOPD,^[11]^ inhibits inflammatory reactions,^[12]^ reduces airway mucus hypersecretion,^[13]^ controls lung infection, and reduces the use of antibacterial drugs.^[14]^ Based on these effects, we intend to further study the heat-clearing and phlegm-resolving effects of TCM on the reduction of the dosage of systemic glucocorticoids. In this trial, the dosage of systemic glucocorticoids will be regarded as the primary endpoint. The secondary endpoints will include: symptom scores, assessed by the COPD assessment test (CAT) scores and modified medical research council dyspnea scale scores (mMRC); exercise tolerance, measured by 6 minute walking distance (6MWD); lung function, measured by forced expiratory volume in 1 second (FEV1), the ratio of forced expiratory volume in 1 second to forced vital capacity (FEV1/FVC), and FEV1 as a percentage of predicted value (FEV1%); inflammatory indicators, include C-reactive protein (CRP) and procalcitonin (PCT); length of hospital stay; and symptoms and quality of life scores during the follow-up. The efficacy of TCM in the treatment of AECOPD will be assessed by these indicators.

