### Trial design and oversight

2.1

This will be a prospective, placebo-controlled clinical trial to evaluate the efficacy of TCM in the treatment of patients with AECOPD. A total of 204 eligible patients will be enrolled according to the exclusion and inclusion criteria and randomly assigned to the TCM or placebo group at a 1:1 ratio. The antibiotic group and non-antibiotic group will be set in advance for subgroup analysis. After a 7–14 day intervention and 12 weeks of follow up, the efficacy of TCM in the treatment of patients with AECOPD will be evaluated based on the primary endpoint (the dosage of systemic glucocorticoids [at which CAT scores improve by 50%]) and secondary endpoints (symptoms scores, exercise tolerance, lung function, length of hospital stay, symptoms, and quality of life scores during the follow up). The flow chart of the study is presented in Figure 1.

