### Randomization and intervention

2.6

The randomization protocol will be designed by a member of the Sichuan TCM Evidenced-Based Medicine Center. They will generate 204 random numbers will using SAS 9.2 statistical software (SAS Institute, Cary, NC). Treatment allocation will be conducted by an independent statistician according to the random numbers generated by the statistical software. Eligible patients will be randomly assigned to either the TCM group or the placebo group using sealed opaque envelops after obtaining informed consent. A special manager will record this randomization process. An individual's randomization number and group allocation can be identified by checking the envelope, which will be performed in case of a clinical emergency.

All participants will receive basic Western medical therapy advocated by the Chinese Expert Consensus on the diagnosis and treatment of AECOPD (2017 update),^[8]^ which includes:

1.Controlled oxygen therapy: Venturi mask inhales oxygen.2.Bronchodilators: compound ipratropium bromide solution for inhalation (Laboratoire Unither, Amiens, France), 2.5 mL, inhale, three times a day;3.Phlegm medicine: fudosteine tablets (Pharmaceutical Co., Ltd.), 0.4 mg, orally, three times a day;4.Glucocorticoids: methylprednisolone sodium succinate for injection (Tianjing Jinyao Pharmaceutical Co., Ltd. Tianjing, China), 40 mg, administered with 0.9% sodium chloride injection (100 mL), intravenously, once a day (depending on the patient's condition, the dosage can be reduced or changed to oral administration, but the longest course of treatment cannot exceed 14 days);5.Antibacterial drugs: according to bacterial resistance and the general course of treatment will be 5 to 7 days, although special circumstances can appropriately extend the application time of antibacterial drugs.

In addition, the TCM group will receive TCM granules (one bag at a time, three times a day) and the Placebo group will receive Placebo granules (one bag at a time, three times a day). Both groups will or will not receive antibiotic treatment according to the antibiotic treatment criteria, which are:

1.During AECOPD, aggravated difficulty breathing, increased sputum volume, and purulent sputum occur simultaneously;2.The patient only has two of the above three symptoms, but has purulent sputum;3.Severe acute exacerbation that requires invasive or noninvasive mechanical ventilation.

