### Prespecified subgroup analysis

2.12

A subgroup analysis will be performed on the use of antibiotics and no antibiotics in the TCM and placebo groups to explore the correlation between antibiotic therapy and the outcomes of the study.

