### Statistical analysis

2.16

Intention-to-treat analysis and per-protocol analysis will be used. Intent-to-treat analysis means that after subjects are randomized, whether they choose to withdraw from the trial or switch to another group, their results are based on their initial grouping during data analysis. Intention-to-treat analysis will be used to analyze completed cases and dropout cases. Efficacy analysis adopts per-protocol analysis; thus, it kicks out those cases with insufficient compliance during the analysis and analyzes only the completed cases. When there is a difference between the two results, the difference will be discussed and explained.

We will use SPSS 19.0 statistical software for statistical analysis. The measured value of the data will be expressed as mean ± standard deviation. If the data follow the normal distribution and the variance is homogeneous, the *t* test will be used; however, if the data does not follow the normal distribution or the variance is uneven, the Wilcoxon rank-sum test will be sued. The Bonferroni method will be used to further compare the differences between antibiotic and non-antibiotic subgroups to explore whether antibiotics will affect the outcomes. The Chi-square test will be used for counting data and rank-sum test will be used for ranking data. All tests will be two-sided, with *P* < .05 being considered statistically significant.

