One of the advantages of this test is that it facilitates the observation of the reduction of glucocorticoid dosage as the main outcome indicator. The dosage of glucocorticoids can be adjusted by changing the CAT score, which has guiding significance for regulating the use of clinical glucocorticoids. Secondly, this trial pre-sets a subgroup analysis based on the need for antibiotic treatment, which is in line with the clinical practice of antibiotic use. The shortcomings of this trial are that the TCM intervention time for AECOPD patients is short, which may affect the expected results, as prolonging the patient's treatment time with TCM may be beneficial to patient condition and prognosis. However, the results of this study are only applicable to a single AECOPD patient group with phlegm-heat congested lung syndrome. It will still be unknown whether patients who do not meet this syndrome can be effectively treated using the same TCM. A final disadvantage is that samples will be gathered from a single center only, which will reduce the applicability and generalizability of the results.

The purpose of this test is to observe whether the TCM for clearing heat and resolving phlegm can reduce the dosage of glucocorticoids in hospitalized patients and provide more evidence for the treatment of AECOPD by TCM.

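### The Bonferroni comparison of antibiotic with non-antibiotic patients cannot show whether antibiotics affect outcome or whether the TCM effect differs, and the subgroup is defined inconsistently

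*Protocol article*

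**What the plan says.** All references are to the protocol article.

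- **Method and aim (2.16 Statistical analysis).** "The Bonferroni method will be used to further compare the differences between antibiotic and non-antibiotic subgroups to explore whether antibiotics will affect the outcomes". No treatment-by-subgroup interaction is named in that section.
- **Subgroup as use (2.12 Prespecified subgroup analysis).** "A subgroup analysis will be performed on the use of antibiotics and no antibiotics in the TCM and placebo groups". The aim given there is a correlation of antibiotic treatment with outcome.
- **Subgroup as set beforehand (2.1 Trial design and oversight).** "The antibiotic group and non-antibiotic group will be set in advance for subgroup analysis".
- **Subgroup as need (3 Discussion).** "this trial pre-sets a subgroup analysis based on the need for antibiotic treatment". The Discussion lists this among the trial's advantages.
- **Who gets antibiotics (2.6 Randomization and intervention).** "Both groups will or will not receive antibiotic treatment according to the antibiotic treatment criteria". The criteria are three cardinal symptoms together, or two of them including purulent sputum, or "Severe acute exacerbation that requires invasive or noninvasive mechanical ventilation". No time of assessment is given.
- **Rationale (1 Introduction).** Heat-clearing, phlegm-resolving TCM is said to be a treatment that "controls lung infection, and reduces the use of antibacterial drugs".

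**The concern.** Three things are tangled in this analysis.

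1. **The contrast.** Patients who receive antibiotics do so because they have purulent sputum, more symptoms or a need for ventilation. A difference in glucocorticoid dose or CAT score between them and the others mixes any antibiotic effect with the reason for prescribing.
2. **The tool.** A subgroup analysis in a two-arm trial should ask whether the TCM effect differs between subgroups. Bonferroni only sets a stricter threshold for each of several tests.
3. **The definition.** Use, need and a grouping set in advance can be different sets of patients. If membership is settled by what happens after randomisation, the arms within a subgroup are no longer comparable.

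At stake is a published statement about antibiotics, or about TCM with and without antibiotics, that the design cannot support.

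**Working it through.** **1. The passages side by side.**

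| Section | Subgroup is | Time fixed |
|---|---|---|
| 2.1 | antibiotic and non-antibiotic groups | in advance (of what is not said) |
| 2.6 | patients meeting or not meeting criteria | not stated |
| 2.12 | use or no use | not stated |
| 3 Discussion | need | analysis pre-set; time of judging need not stated |

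These agree only if the criteria are assessed once, before randomisation, and use follows them exactly. The ventilation criterion strains that reading. It includes invasive ventilation, yet 2.4 excludes patients who require it, so an enrolled patient can meet that branch only by later deterioration.

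**2. Size of confounding by indication (illustration).** The protocol gives no figure for the subgroup analysis, so there is none to reproduce.

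- SD from 2.5 (31.1 and 32.9 mg): √((31.1² + 32.9²)/2) = 32.0 mg.
- Assumed: latent severity is standard normal; its correlation ρ with dose is 0.3 to 0.7; the sickest share p receives antibiotics; antibiotics have no effect on dose.
- Mean severity is φ(c)/p among users and −φ(c)/(1−p) among non-users, where c is the cut-off. At p = 0.70 these are 0.497 and −1.159, a gap of 1.656.
- Dose gap = ρ × 32.0 × 1.656, which is 15.9 mg at ρ = 0.3 and 37.1 mg at ρ = 0.7.

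This gap arises with no antibiotic effect. It would be smaller if prescribing tracked severity less tightly.

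**3. What Bonferroni does.** The per-test level becomes 0.05/2 = 0.025 for two comparisons, or 0.05/4 = 0.0125 for four. Neither removes the gap in step 2, and neither estimates a difference between TCM effects.

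**4. If actual use defines the subgroup.** Same model, with no TCM effect on dose, but TCM assumed to lower use from 70% to 50%. At p = 0.50 the mean severities are 0.798 and −0.798.

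- Users, TCM minus placebo: ρ × 32.0 × (0.798 − 0.497) = 2.9 mg (ρ = 0.3) to 6.7 mg (ρ = 0.7).
- Non-users: ρ × 32.0 × (−0.798 + 1.159) = 3.5 mg to 8.1 mg.

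TCM looks worse in both subgroups although it does nothing to dose. If the split is fixed at baseline, so that the share is equal in both arms, the bias is 0.

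**5. What an interaction test can detect.** With 87 evaluable patients per arm, SE = 32.0 × √(2/(87p) + 2/(87(1−p))). The smallest interaction detectable with 80% power at two-sided 0.05 is 2.80 × SE.

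| Assumed antibiotic share | SE (mg) | Detectable interaction (mg) |
|---|---|---|
| 50% | 9.7 | 27.2 |
| 70% | 10.6 | 29.7 |
| 80% | 12.1 | 34.0 |
| 90% | 16.2 | 45.3 |

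For comparison, the overall TCM effect detectable with 87 per arm at this SD is 2.80 × 32.0 × √(2/87) = 13.6 mg. An interaction of that size would have about 29% power at a 50% share and 13% at 90%.

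**The case against.** **The subgroup may be a baseline factor.** A reader might infer from 2.12 that membership is certainly antibiotic use after randomisation, and that the within-subgroup TCM effects are therefore biased. The documents do not establish this. Section 2.1 has the groups set in advance and the Discussion speaks of need; if need is judged before randomisation, nothing is conditioned on treatment. The Introduction's remark on antibacterial use reports cited literature and may mean shorter courses, not fewer patients starting. This objection stands: selection after randomisation is a plausible risk. It remains plausible because 2.12, the section that specifies the analysis, says use; 2.6 gives no assessment time; and setting groups in advance may mean only that the analysis was prespecified.

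**The false-contrast risk cannot be sized from the protocol.** A reader might also infer a large chance that TCM is significant in one subgroup and not in the other. That needs overall power of exactly 80% and equal halves. The inputs in 2.5 (a difference of 256.7 − 187.6 = 69.1 mg, SD about 32 mg) imply far more power, and the article states no such decision rule. No such figure is claimed here.

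**The interaction model may be in a SAP.** A missing model term alone would be no finding in a condensed article. Here, however, the article states a method, a contrast and an inference, and the inference does not follow from the other two.

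**The analysis is exploratory.** True, and it limits the priority. Exploratory status does not make a confounded contrast informative about antibiotics.

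**Conclusion.** The point holds, in two parts of different strength.

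- **Firm:** comparing antibiotic with non-antibiotic patients is confounded by indication however and whenever the subgroup is defined, and Bonferroni is not a test of effect modification. The stated question cannot be answered this way. The 16 to 37 mg gap rests on the assumed 70% share, the assumed correlations and prescribing fully determined by severity; the documents give none of these.
- **Moderate confidence:** the definition is inconsistent across 2.1, 2.12 and the Discussion. If actual use is meant and TCM changes it, the within-subgroup TCM effects are biased, by about 3 to 8 mg under the assumptions shown; if the split is fixed at baseline, by nothing.

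The primary comparison is untouched. This should be corrected, but it does not threaten the main result.

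**What to change.** 1. Reconcile 2.1, 2.12 and the Discussion: define the subgroup as whether the protocol's existing antibiotic criteria are met at baseline, recorded on the CRF before randomisation. This sets an analysis variable only and does not alter who is treated.
2. In 2.16, replace the Bonferroni comparison with a treatment-by-baseline-indication interaction estimate, and give the TCM-placebo difference with 95% CI in each subgroup, labelled exploratory.
3. Report antibiotic use by arm descriptively.
4. Remove the aim of judging whether antibiotics affect the outcomes, and draw no conclusion on it.

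Cost: one CRF item and revised wording; 2.14 already has baseline information collected before randomised treatment. Downside: the interaction test has low power, as shown above, and stays exploratory.

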## Discussion

3

COPD has a “high morbidity and high mortality rate” worldwide, and has become a major problem for medical treatment. In particular, the acute deterioration of respiratory symptoms during the acute exacerbation period poses a serious threat to health and requires additional treatment. The 2019 GOLD guidelines state that the cause of the acute exacerbation of COPD is often respiratory infections and affirm the therapeutic role of systemic glucocorticoids in the acute phase: improving patient lung function, increasing oxygenation, and shortening hospitalization and recovery time.^[5]^ However, systemic glucocorticoids cause a variety of adverse reactions such as hyperglycemia, hypertension, osteoporosis and femoral head necrosis, and gastrointestinal bleeding and higher doses of glucocorticoids cause a higher risk of adverse reactions.^[19]^ Therefore, glucocorticoids have become a topic of concern. Whether TCM can reduce the dosage of glucocorticoids is worth research.

Currently, there are a small number of research reports on the efficacy of TCM for the reduction of the dosage of glucocorticoids in patients with AECOPD.^[20–22]^ However, these reports use small sample size and do not use the reduction in glucocorticoids dosage as the primary outcome indicator. There is no high-quality clinical evidence of randomized, blinded, and large samples. Thus, in this test, the reduction of glucocorticoids dosage will be regarded as the primary outcome to evaluate the effect of the TCM in reducing the dosage of glucocorticoids for the treatment of AECOPD.

One of the advantages of this test is that it facilitates the observation of the reduction of glucocorticoid dosage as the main outcome indicator. The dosage of glucocorticoids can be adjusted by changing the CAT score, which has guiding significance for regulating the use of clinical glucocorticoids. Secondly, this trial pre-sets a subgroup analysis based on the need for antibiotic treatment, which is in line with the clinical practice of antibiotic use. The shortcomings of this trial are that the TCM intervention time for AECOPD patients is short, which may affect the expected results, as prolonging the patient's treatment time with TCM may be beneficial to patient condition and prognosis. However, the results of this study are only applicable to a single AECOPD patient group with phlegm-heat congested lung syndrome. It will still be unknown whether patients who do not meet this syndrome can be effectively treated using the same TCM. A final disadvantage is that samples will be gathered from a single center only, which will reduce the applicability and generalizability of the results.

The purpose of this test is to observe whether the TCM for clearing heat and resolving phlegm can reduce the dosage of glucocorticoids in hospitalized patients and provide more evidence for the treatment of AECOPD by TCM.
